### **2.3.2 Clinical studies**

Efficacy and safety of NeuroAiD in both healthy controls and stroke patients were reported by Gan et al. (20), both the immediate and long-term effects of NeuroAiD were tested. In the article three studies are reported which revealed that there were no statistically or clinically significant differences in haemostatic, haematological or biochemical parameters due to NeuroAiD. These safety findings were supported in a subsequent study by Young et al (17) in 114 stroke patients

where they revealed that there were no statistically or clinically significant differences in biochemical and haematological parameters or on electrocardiogram tests between participants taking the NeuroAiD and taken placebo at 3 months. On the other hand, there is evidence suggesting a beneficial effect of NeuroAiD on cerebral blood circulation and functional outcomes post-stroke. To explore the possible impact of NeuroAiD on cerebral blood flow, a study was conducted with 80 patients post-stroke (15). It was revealed that participants taking NeuroAiD demonstrated increased cerebral blood flow velocity in comparison to placebo. It was also observed that participants taking NeuroAiD had higher scores of a measure of everyday functioning (Barthel Index).

Other studies have explored the influence of NeuroAiD on functional outcomes, including a small clinical trial conducted with 40 patients one month following stroke (18). Trends in improvement of limb functioning were observed in the NeuroAiD group in comparison to placebo. The frequency of reporting of adverse events was equal between groups and all events were classified as mild or moderate in severity. Subsequently a study was completed in Iran with 150 patients up to 1 month post-stroke which revealed that participants taking NeuroAiD for 3 months showed improved scores on motor functioning in comparison to those taking placebo capsules (16). A larger study of NeuroAiD in a pooled sample of 605 patients post-stroke also demonstrated trends in improvement in physical functioning in participants taking NeuroAiD (12). However this study has some methodological limitations that impact on the interpretation of the results e.g. the control group took an active alternative Chinese medicine (Buchang Naoxintang Jiaonang).

Two studies of NeuroAiD II™ (MLC901) in patients after acute ischemic stroke have been reported (36) with treatment duration of 1 and 3 months (Protocols [#EFSA2011\\_01](#), [EFSA2014\\_04](#), 36,49,50). After one month of treatment, MLC901 in addition to standard treatment and early rehabilitation after a stroke was associated with better improvements in neurological, cognitive, functional, emotional, and disability parameters compared to standard treatment and rehabilitation alone (36,49):

- NIHSS (National Institutes of Health Stroke Scale; 0 - No stroke symptoms, 1–4 Minor stroke, 5–15 Moderate stroke, 16–20 Moderate to severe stroke, 21–42 Severe stroke),
- MMSE (Mini-Mental Status Examination; questionnaire to measure cognitive impairment),
- BI (Barthel Index; ordinal scale of performance in activities of daily living),
- Rehabilitation Activities Profile (assessment of communication, mobility, personal care, occupation, and relationships, based on International Classification of Impairments, Disabilities and Handicaps)
- HADS (Hospital Anxiety and Depression Scale)

In an observational study, after a 3-month course of MLC901 as add-on treatment to standard rehabilitation therapy, an association between the use of MLC901 and recovery was detected. Multivariate analyses identified baseline Barthel Index score, time to treatment, and MLC901 to be positive predictors of improvement. Among patients with more severe stroke (NIHSS >14), more patients who received MLC901 showed above-median improvements on mRS (modified Rankin Scale; measures the degree of disability or dependence in the daily activities of people after stroke) compared to those who did not, at month 1 (71.4% vs. 29.4%;  $p = 0.032$ ), and a similar trend was retained at month 3 (85.7% vs. 50%;  $p = 0.058$ ).

A pilot study by Theadom et al. (21) of NeuroAiD II™ (MLC901) in N=78 adults with impaired CFQ at baseline revealed significant improvements [as measured by Cohen's d effect size] in

complex attention ( $P=0.04$ ) and executive functioning ( $P=0.04$ ) following mild to moderate TBI following 6 months of treatment compared to controls. Additionally, there was a small improvement in the cognitive domain of quality of fatigue. As few participants experienced physical functioning deficits following TBI, a ceiling effect on the GOS-E measure was noted. There were no trends in effect noted for fatigue. It was concluded that a full scale, multi-centre clinical trial is needed to determine clinical efficacy of NeuroAiD II™ (MLC901) in adults following TBI on cognitive functioning, symptoms and quality of life.

Another study by Al Fauzi et al. (22), called Neurological Prognosis after brain Trauma and Use of NeuroAiD™ (NEPTUNE) in a population of  $N=32$  adults, aimed to assess the effects of MLC601 on the functional and neurological outcome of patients with non-surgical moderate TBI (GCS 9 to 13) when given within 2 days of injury. All patients were followed for 6 months. On Barthel Index, the MLC601 group had higher median values compared to the control group at all time points, reaching significance at month 3 (47.5 vs. 35.0;  $p = 0.014$ ) and at month 6 (67.5 vs. 57.5;  $p = 0.055$ ). Trajectories of BI over time showed significant improvement of Barthel Index in the MLC601 group from time of discharge to month 3 to month 6 (40.0 to 47.5 to 67.5, respectively).

Safety pharmacology of NeuroAiD (MLC601) and NeuroAiD II (MLC901), both from clinical studies and spontaneous reports from markets, is detailed in the Investigator's Brochure, Section 5.3. Clinical Safety. By now, no data suggesting negative influence of NeuroAiD (MLC601) and NeuroAiD II (MLC901) on the cardiovascular, respiratory and central nervous system or specific types of toxicity has been reported. Data from clinical studies confirm that NeuroAiD does not affect blood hematology, blood biochemistry and hemostasis, ECG parameters, renal and liver functions (12,16,17,20,36).

In the reported clinical studies of NeuroAiD I or II occurrence of adverse events in patients receiving NeuroAiD was not higher than AE occurrence in the control group. Among adverse events, the more commonly reported with treatment were predominantly gastrointestinal, e.g., nausea, vomiting, diarrhea, and abdominal discomfort, which may be attributable to the number of capsules taken per day, i.e., 4 capsules three times a day for MLC601 and 2 capsules three times a day for MLC901. Allergic reactions and gastrointestinal tract reactions are expectable due to the herbal nature of the drug. However, according to clinical data, they were rather rare and mild.

Due to severity of underlying neurological diseases (including stroke, dementia) serious adverse events were recorded in the studies of NeuroAiD. There was no overall increase in serious adverse events reported, they were mostly related to complications of the underlying disease.

Two clinical studies demonstrated clinical safety of MLC601 in healthy subjects and stroke patients: MLC601 did not modify hemostatic, hematological, and biochemical parameters in normal subjects (43 patients) and stroke patients (10 patients) (20). Patients after ischemic stroke received MLC601 in addition to aspirin and other standard medications for associated medical conditions, such as diabetes mellitus, hypertension, hypercholesterolemia, and ischemic heart disease. No significant differences were observed in hemostatic, hematological, and biochemical parameters tested at 1 and 4 weeks compared to baseline.

In a safety study (80 patients with ischemic stroke received MLC601) there was no statistical difference in hemoglobin, creatinine, sodium, potassium, ALT and AST at the different specified timepoints up to 6 months (39).

Reports of open-label use in stroke patients observed low rates of adverse events, with only 4 cases (of which only 2 were considered likely related to treatment: diarrhea and “heatiness”) among 24 patients, and only 3 “side effects” reported as reason for discontinuing treatment among 192 patients (19,40).

Earlier completed randomized controlled studies reported very low rates of adverse events in the study treatment group which were not different from the active control or placebo group (12,15,16,18,41,39).

The randomized, double-blind, placebo-controlled CHIMES Study randomized 1099 patients from Singapore, Philippines, Thailand, Malaysia, Hong Kong and Sri Lanka who suffered an ischemic stroke of intermediate severity within 72 hours to either MLC601 4 capsules 3 times a day or matching placebo for 3 months (42,43). The first 114 subjects were included in a clinical and laboratory safety study (17). Occurrences of adverse events (AEs) were similar between the treatment groups and were commonly related to the underlying stroke. There were no statistically significant differences between treatment groups in all the hematology tests at 3 months.

At the end of the CHIMES Study, 542 patients on MLC601 and 545 on placebo were included in the safety analysis. 230 (42%) subjects on MLC601 reported 459 AEs compared to 218 (40%) subjects on placebo reporting 504 AEs. The frequency of MedDRA preferred terms by system organ class is provided in IB (36, Section 7 Appendix).

The pre-planned CHIMES-E extension study (EFSA2007\_04) followed up CHIMES patients (n=880) up to 2 years from study inclusion (44,45). While no further treatment was given apart from standard stroke therapies and rehabilitation, it provided further opportunity to assess the long-term efficacy and safety of MLC601 even after the study treatment was already discontinued. The study showed that by month 24, rates of death and occurrence of any vascular event and other medical events classified according to organ system were similar between treatment groups. In particular, there was no difference in the rates of renal or hepatic adverse events. Neoplasm was reported in 4 subjects each for the MLC601-treated (gynecologic 1, lung 2, urinary 1) and placebo-treated (parathyroid 1, lung 2, urinary 1) groups.

*Table 2.3. Number of patients experiencing medical events over 24 months in the CHIMES-E Study (44,45)*

| Medical Events                       | MLC601 (n=446) | Placebo (n=434) |
|--------------------------------------|----------------|-----------------|
| Death                                | 28 (6.3%)      | 29 (6.7%)       |
| Vascular event*                      | 56 (12.6%)     | 55 (12.7%)      |
| Central nervous system, non-vascular | 24 (5.4%)      | 19 (4.4%)       |
| Cardiac, non-vascular                | 5 (1.1%)       | 3 (0.7%)        |
| Hepatobiliary                        | 2 (0.4%)       | 2 (0.5%)        |
| Renal                                | 10 (2.2%)      | 9 (2.1%)        |
| Hematologic                          | 12 (2.7%)      | 8 (1.8%)        |
| Dermatologic                         | 2 (0.4%)       | 0 (0.0%)        |
| Endocrine                            | 9 (2.0%)       | 5 (1.2%)        |
| Gastrointestinal                     | 18 (4.0%)      | 16 (3.7%)       |
| Gynecologic                          | 2 (0.4%)       | 0 (0.0%)        |
| Infection                            | 23 (5.2%)      | 26 (6.0%)       |
| Ophthalmologic                       | 0 (0.0%)       | 1 (0.2%)        |
| Orthopedic                           | 7 (1.6%)       | 7 (1.6%)        |
| Psychiatric                          | 4 (0.9%)       | 1 (0.2%)        |
| Pulmonary                            | 3 (0.7%)       | 6 (1.4%)        |

| Medical Events | MLC601 (n=446) | Placebo (n=434) |
|----------------|----------------|-----------------|
| Rheumatologic  | 6 (1.3%)       | 7 (1.6%)        |
| Urinary        | 5 (1.1%)       | 6 (1.4%)        |

\* Recurrent stroke or transient ischemic attack, acute coronary event, pulmonary embolism, peripheral vascular disease, sudden death

In a recent clinical study of NeuroAiD II™ (MLC901) in patients with mild TBI, NeuroAiD II™ (MLC901) was found to be safe and well tolerated in TBI patients (21). In the 36 patients with mild TBI who received NeuroAiD II™ (MLC901), 3 adverse events were observed: headache in 1 patient, sore tongue in 1 patient, itchiness in 1 patient. Hematuria due to a secondary medical condition was observed in one patient. In the Placebo group, consisting of 42 patients, adverse events included difficulty sleeping, headache, itchiness and upset stomach. These adverse events were minor. No serious adverse events were reported.

Moleac's pharmacovigilance database reveals that only minor side effects have been reported including: nausea, vomiting, diarrhoea, dizziness, headaches, dry mouth, digestive discomfort (due to the high herbal concentration), and various allergic reactions with similar findings in the published clinical trials reviewed (16-19). Of all serious adverse events observed in the clinical trials post-stroke "all events were commonly observed post-stroke including stroke progression, recurrent stroke and cardiac events" (17).

Details of clinical and preclinical studies of IP are provided in the IB (36).

## 2.4 Summary of the Known and Potential Risks and Benefits, if any, to Human Subjects

Risks to subjects in this study are related to:

- common procedures performed
- documented adverse events listed in the current reference products information.

These risks are communicated to the subjects in the consent forms.

Based on the safety profile of NeuroAiD II™, the risks through participating in the trial are considered low. Clinical safety data from MLC601 and MLC901 showed no overall increase in adverse events, most commonly reported AEs upon treatment were predominantly gastrointestinal, e.g. nausea, vomiting, diarrhea, and abdominal discomfort, which may be attributable to the number of capsules taken per day. The detailed list of expected events, that have been observed after IP administration in previous studies, is given in the respective section of IB (36).

Risks for subjects related to study procedures required by this protocol are minimal. The risk of participating in this clinical trial, similar to other trials, is related to blood drawing via venipuncture. Although hardly probable but there exists a possible risk of infection during blood sampling procedure. This risk can be eliminated by professionally performed procedure with qualified professional medical staff.

The total blood draw volume in this study is no more than 20 ml, which will be taken twice (in the beginning of the study and upon completion). Normal blood donation volume is up to 500 mL for one procedure, therefore the blood volume drawn in this study is incomparably lower than upon blood donation and there is no risk for volunteers in comparison to blood donation procedure.

The patients recruited in both NeuroAiD II™ and placebo are not in severe condition and are allowed to receive any other mTBI treatment besides IP. On the other hand, patients, receiving

placebo, avoid the risks, associated with IP intake and possible AEs, produced by its active substances.

Current study incorporates several measures to mitigate risks:

- measures will be taken during screening to ensure safety of the study subjects;
- the protocol specifies medical surveillance over the patients which includes recording and evaluation of AEs;
- in case of a known adverse reaction to the drug product, the investigator will take all the necessary actions, including discontinuation of the drug product;
- qualified personnel will perform the procedures in the scope of this study.

The benefit for the patient from participation in this clinical trial includes:

- thorough multiple-scale diagnostics of patient's condition after TBI;
- surveillance of dynamics of patient's condition for 9 months – during the study and follow-up period.

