| Compliance assessment                                                                     |                        |                            | X        | X         | X          | X                            |
| Adverse Event
Monitoring                                                               |                        | X                          | X        | X         | X          | X                            |
| Investigational product
supply                                                         |                        | X                          | X        | X         |            |                              |
| Study drug administration                                                                 |                        | Day 1 – Day 180±14 days    |          |           |            |                              |

 Informed Consent Form must be obtained prior to performing any study-related procedures;  
 Body weight and height will be obtained without outerwear and shoes; BMI = weight (kg)/height (m^2)

 Subjects will be randomized just prior to dosing. Further drug intake will be done according to the randomization scheme.

\* Not necessary if complete information was obtained upon Screening

\*\* Not necessary if screening (visit 1) and randomization (visit 2) are performed on the same day (which will be Day 1).

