### 8.2 Methods and Timing for Assessing, Recording, and Analyzing Safety Parameters

The corresponding safety endpoints are:

1. Number of TEAEs, recorded during the Study period (Day 1 – Day 270±30) in the NeuroAiD II™ group and in the Placebo group
2. Number of ADRs, recorded during the Study period (Day 1 – 270±30 days) in the NeuroAiD II™ group and in the Placebo group
3. Number of SAEs, recorded during the Study period (Day 1 – 270±30 days) in the NeuroAiD II™ group and in the Placebo group
4. Number of patients who discontinued treatment in the NeuroAiD II™ group and in the Placebo group
  - Due to AE
  - For any reason
5. Number of clinically significant (assessed by the Investigator) deviations in the results of haematology, blood chemistry and urine laboratory tests upon NeuroAiD II™/Placebo treatment completion (Day 180±14) in the NeuroAiD II™ group and in the Placebo group compared to baseline (data of laboratory tests and ECG performed at Screening)

At each study visit, the Investigator will ask patients about their well-being and assess whether any subjective AEs have occurred. The AEs, TEAEs, SAEs and ADRs will be recorded starting from the first IP dose intake (Day 1). Subjects may report to the Investigator the AEs occurring at any other time during the study. All subjects experiencing AEs, whether considered associated with the use of the study drug or not, must be monitored until resolution or stabilization.

Procedures for physical examination, vital signs assessment, 12-lead ECG and laboratory tests were detailed in Section 4. The physical examination results, as well as any changes that have occurred since the last inspection should be described in the primary documents and CRF. Data of physical examination, laboratory tests, vital signs and ECG data will be categorized as “normal”, “abnormal, clinically not significantly” or “clinically significant abnormal”. The clinically significant deviations in results of laboratory or instrumental assessment and physical examination data, vital signs and ECG data should be registered as AEs in eCRF.

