### 8.3.4 Documentation and reporting of adverse events

All AEs will be documented in the AE page of the CRF, whether or not the investigator concludes that the event is related to the drug treatment. The following information will be documented for each event:

- Event term (preferably, diagnosis).
- Dates of the beginning and the end of AE.
- Frequency: intermittent, continuous.
- Severity: CTCAE grades
- Causal relationship between the event and administration of study drug or study procedure (not related, conditional, unlikely related, possibly related, probably related, definitely related, not applicable).
- Action concerning study drug (drug withdrawn, dose not changed, dose reduced/increased, unknown, not applicable).
- Outcome of event (recovered, recovering, not recovered, resolved with sequelae, fatal, unknown).
- Seriousness (serious, non-serious).

Information on TEAEs and SAEs will be received by all members of the Study team.

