#### 8.3.4.1 SAE reporting

When an SAE occurs through the AE collection period it should be reported according to the following procedure:

As soon as the Investigator is aware of SAE, he/she:

- immediately registers information in patient's medical file,
- immediately (or within 24 hours of first onset or notification of the event) completes and signs the SAE form and sends it to Atlant Clinical by fax or e-mail (e-mail: [[contact]](mailto:[contact]), contact information will also be given in the Investigator study file):

Concerning any safety aspects, the Atlant Clinical medical monitor should be contacted:

Name: [name]

Position: Medical Monitor

[contact]

[contact]

[contact]

e-mail: [[contact]](mailto:[contact]), [[contact]](mailto:[contact]).

In the SAE form the information should be completed as fully as possible but contain at a minimum:

- A short description of the event and the reason why the event is categorized as serious.
- Subject identification number.
- Investigator's name.
- Name of the study drug

In case of SAE, the Sponsor must also be notified either by the Investigator or by Atlant Clinical within 24 hours after the Investigator/CRO is aware of the SAE:

Name: [name]

Position: Senior Medical Advisor

[contact] Ext 182

Tel. (mobile): [contact]

e-mail: [[contact]](mailto:[contact])

Any follow-up information on SAE should be notified within 24 hours via the SAE form (the procedure should be the same as described above). If a non-serious adverse event becomes serious, or if an adverse event becomes a suspected fatal/life-threatening adverse reaction, the procedure should be the same as described above.

For SAEs, the Investigator will send to Atlant Clinical anonymized copies of additional medical documents with relevant information on the event in the same way as described above. Upon SAE completion the final SAE report form should be filled and sent to Atlant Clinical by e-mail: [[contact]](mailto:[contact]) or by [contact]

Atlant Clinical will immediately transmit to the Sponsor the forms and documents received from the Investigator (within 24 hours after the information was received by CRO).

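### AE and SAE recording starts at the first dose, so no rule requires an event between consent and first dose, including one caused by a screening procedure, to be recorded or reported

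*Protocol*

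**What the plan says.** Section 2.4 of the protocol treats blood sampling as the procedural risk: "The risk of participating in this clinical trial, similar to other trials, is related to blood drawing via venipuncture". It mentions infection as an unlikely possibility and adds: "This risk can be eliminated by professionally performed procedure with qualified professional medical staff". A list of four general risk-mitigation measures follows, one of which is that "the protocol specifies medical surveillance over the patients which includes recording and evaluation of AEs".

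Three places set the start of safety collection, and they agree:

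- Section 8.2: "The AEs, TEAEs, SAEs and ADRs will be recorded starting from the first IP dose intake (Day 1".
- Table 1.1 (section 1.3): the row "Adverse Event Monitoring" is marked from Visit 2 to Visit 6 and is empty at Screening. A footnote says "Subjects will be randomized just prior to dosing".
- Section 8.3.4.1: "When an SAE occurs through the AE collection period it should be reported according to the following procedure".

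Other parts of the protocol reach further back or wider. Section 4.4 counts participation from the screening visit. Section 4.1.1 places the first laboratory sampling at Screening, once eligibility is confirmed. Section 8.3.4 requires each AE entry to state the "Causal relationship between the event and administration of study drug or study procedure". Section 5.4 cancels further follow-up for a patient who took no dose and left the study for any reason.

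**The concern.** A person who has signed the consent form and been bled for the trial is already exposed to trial procedures. The protocol accepts this: it counts that time as participation, describes venipuncture as a risk, and provides a causality field for study procedures. The collection window opens later, however, at the first capsule. If a screening procedure caused a serious event on, say, Day -5, no rule would require an AE entry or a 24-hour SAE report. The follow-up duties in sections 5.6 and 8.4 would have nothing to attach to, because they apply to AEs and SAEs, and section 8.2 does not yet call for either to be recorded. If that person then left before dosing, section 5.4 would end follow-up.

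What is at stake is whether harm from the trial's own procedures reliably reaches the sponsor. The treatment comparison is not at stake. An analysis plan cannot repair the gap, because it cannot recover events that were never collected.

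**Working it through.** The protocol gives no figure for this point, so the check sets its sections side by side, with simple counts.

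**1. When does participation start?** Section 4.4 gives a maximum of 314 days from the screening visit. The visit windows reproduce this: 14 (screening) + 270 + 30 (latest End-of-Study visit) = 314. The 14 screening days are therefore inside participation as the protocol defines it.

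**2. When does recording start?** At the first dose on Day 1 (section 8.2; Table 1.1 agrees). SAE reporting under section 8.3.4.1 uses the same period.

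**3. How long is the gap?** Up to 14 days. It falls to 0 days when Visits 1 and 2 are held on the same day, which a footnote to Table 1.1 allows.

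**4. Which procedures fall in the gap?** Physical examination, vital signs, ECG and the first blood draw (section 4.1.1). The draws are consistent with section 2.4: (5 mL haematology + 5 mL chemistry) × 2 occasions = 20 mL, the stated maximum. Of the two draws:

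- The first (about 10 mL) is at Screening, before any dose and outside the window.
- The second is inside the window whether it is taken at Visit 5 (Table 1.1) or at End-of-Study (section 4.1.1, laboratory tests).

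So 1 of 2 scheduled draws per randomized patient precedes the window.

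**5. Who never enters the window?** Section 9.2 allows up to 364 people to be screened for 182 randomized, so up to 364 − 182 = 182 could be screened and never dosed. This is an upper bound on people, not on blood draws. Section 4.1.1 puts laboratory tests after confirmation of eligibility, and the protocol does not say how many screen failures would be bled.

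**6. Does any other text close the gap?**

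| Text | What it does | Duty to record or report pre-dose events? |
|---|---|---|
| Section 8.2, subjects may report AEs occurring at other times | Permits a patient to speak up | No duty on the site |
| Section 4.1.1, AE information collected at Visit 2 | May bring an event to light | Does not move the start date back, and misses anyone who never attends Visit 2 |
| Section 5.4, report on withdrawn patients within 24 hours | Gives the patient's status and reason for leaving | Not an AE or SAE report, and applies only if the patient is withdrawn |
| Section 8.3.2 (sponsor), annual summary of all SAEs | Summarizes what was collected | Cannot include what was not collected |

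None of them creates the missing duty.

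**The case against.** The best case for the protocol is that it is consistent. The AE definition in section 8.3.1.1 refers to a subject who has been given a product, and section 8.2, Table 1.1 and section 8.3.4.1 all follow from it. The causality field for study procedures still has a use, because the second draw and all on-treatment visits lie inside the window. Section 2.4 calls procedural risk minimal. This stands: the start date is not contradicted anywhere, and the point is a gap in coverage. It does not answer why trial procedures done after consent should fall outside any reporting rule.

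A reader might infer four stronger things, which the documents do not support.

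- **That AE recording is the protocol's safeguard against venipuncture harm, and fails.** Section 2.4 ties blood sampling to qualified staff. AE recording is one of four general measures, and the section also names product-related adverse events as a risk.
- **That pre-dose events would inflate the TEAE counts.** AE information is collected at Visit 2, and the AE page records onset dates (section 8.3.4), so an event that began before Day 1 can be identified.
- **That most draws, or many person-years, go unobserved.** Such figures need every one of the 364 screened to be bled and to wait the full 14 days. Section 4.1.1 draws blood only after eligibility is confirmed, and screening and randomization may share a day.
- **That such events would certainly stay unknown to the sponsor.** Step 6 of the working shows routes by which one could surface. The supported statement is that no rule requires it.

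**Conclusion.** The point holds as a gap in subject-safety reporting. Between consent and first dose, for up to 14 days, no rule requires an AE or SAE to be recorded or an SAE to be reported. This includes an event caused by a screening procedure, and 1 of the 2 scheduled blood draws per randomized patient lies there. Section 5.4 makes it somewhat worse for those who leave undosed.

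The size in terms of harm is probably small. The protocol gives no rate of procedure-related events, so no expected number of missed events can be calculated, and the interval vanishes for patients screened and randomized on one day. The primary endpoint, the efficacy analysis and the between-arm safety comparison are unaffected. The conclusion rests on reading section 8.2 as it stands and on finding no other section that extends the duty backwards. It is a modest but worthwhile correction.

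**What to change.** Reconcile section 8.2, section 8.3.4.1 and the AE row of Table 1.1 so that collection starts at signature of the informed consent form:

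- Record AEs and SAEs from that point, at minimum SAEs and events related to a study procedure, and apply the 24-hour SAE procedure from the same point.
- Mark Visit 1 in the AE row of Table 1.1.
- State in section 5.4 that its cancellation of follow-up does not override follow-up of a recorded event.
- List events with onset before first dose separately as pre-treatment events.
- Keep the TEAE and ADR endpoints counted from first dose, so that no endpoint changes.

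The cost is amendment wording, one mark in the schedule, slightly more recording at sites and one extra listing. No visit, procedure, sample size or efficacy analysis changes.
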